### Trial design

2.1.

The planned study is designed as a randomized between-subjects trial with two active groups (one intervention group receiving app-based CBT-I for approximately 8 weeks and one filling in a sleep diary for the same time span). The study intervention functions as an add-on intervention so both groups will receive TAU while undergoing study intervention. Therapists at the study centers delivering the TAU interventions will be blind towards study arm allocation of participants.

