### Participants

2.3.

Participants aged between 18 and 55 years will be included in the study if they (1) have experienced a traumatic event within the past three months as measured with Life Events Checklist (LEC-5; Weathers et al., 2013) and show PTSD symptoms (PTSD Checklist for DSM-5 (PCL-5) score above cut-off value of 33) and (2) report on sleep disturbances which evolved or became stronger after the traumatic experience. Participants will be excluded from the study if they (1) take benzodiazepines or benzodiazepine receptor agonists, (2) report on a lifetime diagnosis of psychosis, bipolar disorder or more than two episodes of major depression, (3) have suffered from an alcohol or substance use disorder within the past year, (4) have an IQ < than 80 points, (5) are diagnosed with any systemic or neurological disorder (e.g. dementia), (6) show signs of acute suicidality, (7) are insufficiently able to communicate in German, (8) work in shifts or have had an intercontinental flight crossing two or more time zones within the past 30 days or (9) suffer from sleep apnea.

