### Treatments/interventions

2.6.

Since the intervention is planned as an add-on intervention, all participants will receive TAU in the clinic they are recruited from and are free to use any form of treatment that is offered to them. Due to the multicentre approach, TAU may differ between participants and will be recorded at T1 after the sleep intervention is completed. Potentially different therapeutic approaches in TAU will be included in exploratory data analysis.

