#### Intervention group

2.6.1.

Participants in the intervention group will get access to the sleep app *somnio* which serves as the form of dCBT-I employed in this study. *Somnio* is the first digital health application listed permanently with the German Federal Institute for Drugs and Medical Devices for the treatment of insomnia and therefore approved for prescription by medical doctors and psychologists since 2020 (mementor DE GmbH, Leipzig, Deutschland). It belongs to the best rated dCBT-I (Simon et al., 2023) and has been shown to significantly and long-lastingly improve insomnia (Lorenz et al., 2019; Maurer et al., 2023), as well as epiphenomena such as daytime functioning, quality of life, symptoms of depression and anxiety (Schuffelen et al., 2023). Compliance data and completion rates of 68% are promising as well for *somnio*, even in a heterogeneous real-world sample (Schuffelen et al., 2023) which is indeed slightly lower than some reported compliance rates for CBT-I that is delivered in person. However, with 48–91% there is also a wide range of compliance rates in this intervention type (Mellor et al., 2022) and *somnio*'s data fall completely within that range. One activation code is valid for 90 days and users can access the application via app or web browser. The intervention period for this respective study is planned for approximately 8 weeks. The intervention program consists of 10 educative core- and 6 concomitant-modules which are based on Morins microanalytic model of insomnia (Morin, 1993a). In this model, it is stated that insomnia is primarily sustained by a cycle of self-perpetuating factors such as high arousal, negative consequences, maladaptive habits and dysfunctional cognitions about sleep (Perlis et al., 2005). Users are guided through the intervention program by an animated sleep coach called Albert to create a tailored dialogue that is based on pre-programmed input by CBT-I experienced psychotherapists. A list and description of all educative modules and the closing session can be found in Table 1.

**Table 1. T0001:** Content of dCBT-I application somnio.

Module	Content description
Introduction	Introduction to therapy content and procedure, personalization of settings, recording of sleep symptoms and therapy goals
Sleep diary	Introduction to sleep diary as basis for subsequent personalized training and instructions on how to fill in the reports

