#### Control group

2.6.2.

The control group will be asked to fill in a sleep diary in online format (link will be sent by email everyday) for 8 weeks which is the same time span as the *somnio* app is processed by the intervention group. For ethical reasons, we intend to offer a *somnio* app activation code to participants of the control group after study completion, too.

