### Procedure and assessment

2.7.

After the recruitment procedure is completed, participants will provide written informed consent and are randomized to one of the two study conditions. Participants will then receive a link to an online questionnaire arranged in SoSciSurvey for baseline assessment (timepoint T0). Following baseline assessment, the intervention group will get access to the *somnio* app and receive dCBT-I for the subsequent 8 weeks whereas the control group will fill in an online sleep diary every day (link provided by email). Five weeks after the start of the intervention, participants will receive a phone call to encourage compliance and spot potential issues with the use of the app or sleep diary. Both groups will continue to participate in TAU of the respective clinic without any limitations. After the intervention phase (10 weeks post baseline), all participants will receive a link to a second online assessment (timepoint T1). Additionally, the researchers conducting the study will contact every participant for a phone interview around T1 to gather information about current medication, number, and content of trauma-related outpatient treatment sessions. Six months after baseline assessment, participants will be contacted again and asked to fill in a follow-up assessment (T2). All measures used for the assessments on different time points are listed in Table 2. At all assessments, participants have the possibility to pause filling out the questionnaires in case they become overwhelmed and are allowed to resume at a later point during assessment day.

**Table 2. T0002:** Measures used for the assessments on different time points.

	Pre-intervention	Post-intervention	
	T0	T1	T2
Demographic data	x		
Sleep diary	x	x	x
MCTQ	x		
PSQI	x	x	x
LEC-5	x		
PCL-5	x	x	x
PCTI	x	x	x
CTQ	x		
BDI-II	x	x	x
BAI	x	x	x
WHODAS 2.0	x	x	x

Abbreviations: *BAI*, Beck Anxiety Inventory; *BDI-II*, Beck-Depressions-Inventar; *CTQ*, Child Trauma Questionnaire; *LEC-5*, Life Events Checklist for DSM-5; *MCTQ*, Munich ChronoType Questionnaire; *PCL-5*, PTSD Checklist for DSM-5; *PCTI*, Post-traumatic Cognitions Inventory; *PSQI*, Pittsburgh Sleep Quality Index; *WHODAS 2.0*, WHO Disability Assessment Schedule.

x, Instrument is assessed at respective timepoint.

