One issue, however, inherent to the exploratory nature of the study, is that it is yet unknown, how the specific population of acutely traumatized individuals will react to the CBT-I intervention. There might be unexpected side effects or increased adversity of known CBT-I side effects such as initially increased tiredness during daytime after sleep restriction (Kyle et al., 2011). However, studies using sleep interventions in patients with chronic PTSD do not support this notion (Colvonen et al., 2019; Talbot et al., 2014). Importantly, such side effects will be monitored at T1, patients continue to be seen at the acute trauma clinics and can always seek any additional psychotherapeutic or pharmacological assistance (except for benzodiazepines) that they might need within study protocol. Additionally, the study team is available in case participants have any questions or wish to report adverse events.

There also are some considerations arising from balancing the methodological rigor and the explorative nature of this study. As mentioned before, TAU is likely going to vary across study centers, therapists and a heterogeneous population of patients and therefore needs to be controlled for both by randomization as well as assessment and later use of covariates. While this approach does indeed introduce more variance than in a completely controlled study protocol, it can also be considered a strength of this explorative study. The ‘real-world’ context actually provides a much stronger trial for a novel intervention and will render any potential effects of the CBT-I intervention more meaningful. It might even indicate which other interventions CBT-I is best paired with. The issue of using a multicentre approach in this study can be reflected upon with a similar argument. It will assure wider (e.g. geographical) participation, and therefore greater generalizability and representativeness of results.

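### Current users of the study app or another structured CBT-I programme are not excluded at screening, so some diary controls may already be receiving the tested treatment and the contrast can be diluted.

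*Protocol article*

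**What the plan says.** **Eligibility.** Section 2.3 (Participants) opens its exclusion list with "Participants will be excluded from the study if they (1) take benzodiazepines or benzodiazepine receptor agonists" and continues to item 9, sleep apnea. Shift work and recent long flights are on the list. The study app, other sleep apps and face-to-face CBT-I are not. On the inclusion side, participants must "report on sleep disturbances which evolved or became stronger after the traumatic experience", so insomnia that began before the trauma is compatible with entry. Section 2.2 makes the screening call the point at which these criteria are checked.

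**Availability of the app.** Section 2.6.1 (Intervention group) says it is "approved for prescription by medical doctors and psychologists since 2020".

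**Other treatment.** Section 2.6 says participants "are free to use any form of treatment that is offered to them". Section 2.7 adds: "Both groups will continue to participate in TAU of the respective clinic without any limitations". The Discussion says patients "can always seek any additional psychotherapeutic or pharmacological assistance (except for benzodiazepines"), which is the only exception named.

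**Control arm.** Section 2.6.2 assigns controls to an online sleep diary for 8 weeks and plans to offer an "activation code to participants of the control group after study completion".

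**Blinding.** Section 2.1 says: "Therapists at the study centers delivering the TAU interventions will be blind towards study arm allocation of participants".

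**Recording.** TAU is recorded at T1 (section 2.6). A phone interview around T1 covers medication and the trauma-related sessions attended (section 2.7). Section 2.9 plans to ask whether therapy included sleep interventions, and lists the content of treatment sessions as a covariate and for exploratory analyses.

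**The concern.** The trial compares app-based CBT-I plus TAU with a sleep diary plus TAU. Everyone enrolled has a sleep complaint, and the tested product can be prescribed outside the trial. A site that follows section 2.3 as written would enrol a patient who is partway through the app on prescription, and could then allocate that patient to the diary. The patient would count as a control while receiving the experimental treatment.

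TAU therapists are blind to allocation, so they would not know which of their patients are diary controls when a sleep treatment is suggested. Blinding limits deliberate compensation of controls, but it does not prevent incidental exposure.

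At stake is the size of the difference the trial can show. The sample size in section 2.4 assumes the full f = .25 and makes no allowance for controls who obtain CBT-I elsewhere.

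**Working it through.** **Inputs from the article.** f = .25, power 80%, alpha 5%, required N = 86 for a between-factor effect in a mixed design (section 2.4); two groups, 1:1 (section 2.5); three assessments, T0, T1 and T2 (section 2.9).

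**Assumptions, not in the article.** Correlation between repeated measures rho = 0.5, and a share c of controls who obtain the full CBT-I effect outside the study.

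**Step 1: reproduce the plan's figure.** For the between-factor test with m = 3 measurements, the noncentrality parameter is

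lambda = f² × N × m / (1 + (m − 1) × rho), with df = 1 and N − 2.

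At f = .25, N = 86 and rho = 0.5: lambda = 0.0625 × 86 × 3 / 2 = 8.06. Power is 0.801, and 86 is the smallest even N that reaches 80%. The plan's figure is reproduced. It depends on rho: the same formula gives N = 70 at rho = 0.3 and N = 104 at rho = 0.7.

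**Step 2: dilute the effect.** If a share c of controls has the full effect, the observed difference is (1 − c) times the true one, so f observed = .25 × (1 − c).

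| c (assumed) | f observed | lambda at N = 86 | Power at N = 86 | Evaluable N for 80% power |
|---|---|---|---|---|
| 0% | .25 | 8.06 | 0.80 | 86 |
| 10% | .225 | 6.53 | 0.71 | 106 |
| 20% | .20 | 5.16 | 0.61 | 134 |

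Cross-check: required N grows by about 1/(1 − c)². This gives 86/0.81 = 106.2 and 86/0.64 = 134.4, in line with the last column.

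**Step 3: partial exposure.** If outside users gain only a fraction e of the effect, replace c by c × e. For example, 20% of controls with half the effect equals 10% with the full effect (0.20 × 0.5 = 0.10). The table is therefore an upper bound for each share of exposed controls. It does not model use that ended before entry.

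**Step 4: what the planned recording covers.**
- *Source.* The question in section 2.9 concerns the therapy process. It may pick up an app prescribed within the clinic. It does not clearly reach one obtained elsewhere.
- *Time.* TAU is recorded around T1, 10 weeks after baseline. Table 2 lists no treatment record at T2, six months after baseline, although T2 is in the mixed model. Use between T1 and T2 is therefore not clearly captured.
- *Use in analysis.* Exposure recorded around T1 is a post-randomisation variable. Adjusting for it describes contamination but does not restore the randomised contrast.

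**The case against.** The strongest reply is that unrestricted background treatment is a declared choice. The Discussion defends a naturalistic setting and counts real-world variation as a strength. Under that question, sleep treatment obtained elsewhere is part of TAU. The article nowhere says that controls must never have had CBT-I; section 2.6.2 gives ethical reasons for the later offer of the app. The trial also calls itself an exploratory pilot. Sleep interventions within therapy are surveyed, and treatment content is a planned covariate. Patients are approached at the start of treatment, within three months of the trauma, so being mid-course on the app at that moment may be uncommon.

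Much of this stands, and it rules out several stronger readings that a reader might infer:

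- *That the contrast is in fact diluted.* No uptake rate is given, so only the possibility can be stated.
- *That everyone with past CBT-I should be excluded.* Earlier users are randomised 1:1, and a person treated before the trauma whose sleep then worsened may still respond. Excluding them would narrow the population that the Discussion wants to represent.
- *That an entry rule would keep controls free of CBT-I.* It cannot stop uptake after randomisation while TAU stays unrestricted, and that freedom is deliberate.

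The defence does not cover one case. The Discussion justifies variation in background care. It does not address enrolling as a control someone already taking the experimental treatment. Since section 2.3 is an explicit numbered list, this gap is not merely detail left to a fuller document.

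**Conclusion.** The point holds in a limited form. Section 2.3 allows a current user of the study app or another structured CBT-I programme to enter and be allocated to the diary arm, and the planned survey is only a partial check on exposure outside the study. The contrast can be diluted, by an unknown amount. With 10% to 20% of controls gaining the full effect, power at N = 86 would be 0.71 to 0.61 instead of 0.80. These figures rest on rho = 0.5, on full effect in exposed controls and on shares that the documents do not supply; partial or late use would cost less. The shares also combine use already under way at screening with uptake after randomisation, and an exclusion removes only the former. The change is worth making because it is cheap, not because contamination has been shown.

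**What to change.** 1. Add to section 2.3 an exclusion for current use of the study app or another structured CBT-I programme, asked in the existing screening call.
2. Record earlier use of such programmes at baseline, without excluding for it.
3. In both arms, ask about CBT-I or sleep apps from any source in the week-5 call, in the T1 interview and at T2.
4. Report this use by arm, and keep these participants in the intention-to-treat analysis.

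The cost is one eligibility line, one item each at baseline and T2, and one question in calls that already take place. A small number of otherwise eligible patients would be lost. TAU is not restricted.

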### Sample size

2.4.

The planned sample size is based on calculations in G*Power 3.1.9.7 (Faul et al., 2007). Literature investigating the effect of combined sleep- and trauma-focused therapy on trauma-related symptoms is scarce. Pigeon et al. (2022) report a medium sized effect of CBT-I on trauma-related symptoms measured with the Clinician Administered PTSD Scale (CAPS; Blake et al., 1995) in individuals diagnosed with PTSD after having experienced a traumatic event within the past year. Referring to this finding and being interested in a clinically relevant effect, we chose an effect size of Cohen's *f* = .25 as a basis for power analysis and sample size calculation. Calculations setting the desired power to 80% and the risk of Type I error rate to *α* = 5% resulted in a required sample size of *N* = 86 to be able to detect medium sized between factor effects in a mixed design, provided the assumed effects exists in the investigated population. Considering a dropout rate of 20% from guideline-recommended psychological treatments for post-traumatic stress disorder (Varker et al., 2021) as an orientation for potential attrition rate, we intend to recruit *N* = 52 participants per group. Due to the exploratory nature of this pilot study, we used only our primary outcome measure for sample size calculations.

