### Statistical analysis

2.9.

Statistical analyses will be based on a mixed general linear model design with the two-level between group factor intervention (intervention vs. control group) and the three-level within group factor time (assessments at T0, T1 and T2) for primary and secondary outcome measures to account for both hypotheses tested in this study. A multilevel approach including study centers with their, presumably, differing TAU interventions, is not feasible due to too low a number of study centers at this hierarchical level. However, as discussed below, study centre and TAU interventions will be used as covariates and for exploratory analyses. For the first research question, the interaction between groups and time will be analysed to determine whether PTSD symptom severity differs for the intervention group after receiving the add-on treatment. For the second research questions, sleep disturbance before the intervention will be used to predict PTSD symptom severity at first and second follow-up for both groups. Due to the exploratory nature of this study, analysis will be conducted both with an intention-to-treat and a per-protocol approach, allowing for a comparison of both effect estimates (Gupta, 2011). For intention-to-treat analysis, dropouts will be included with a last observation carried forward strategy. Extreme cases and outliers will be checked for validity and excluded for per-protocol analysis if indicated. Dropouts will be reported with time point and reason in the final results. We intend to include age, gender, severity of trauma (indicated by classification in type-1 and -2 traumata), number of previous traumatic events, content of trauma-related outpatient treatment sessions and recruiting centre as covariates and in further exploratory analyses. Despite our efforts to proactively reduce variance in trauma treatment among participating trauma centers by organizing joint supervisions, we assume there will be left some significant variance that has to be considered in the statistical analyses. The content of trauma-related outpatient treatment sessions will be classified into trauma-focused versus non-trauma-focused therapy elements since it has been shown that in symptomatic acutely traumatized individuals this may cause a significant difference in treatment outcome (Roberts et al., 2019). Furthermore, we will survey whether sleep interventions have been included in the therapy process or not. By this, we intend to control for the most relevant confounding factors arising from between-participant-treatment-differences.

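### The stated 80% power at N = 86 is for the group main effect over all visits, not for the group × time interaction that section 2.9 plans to test

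*Protocol article*

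**What the plan says.** Section 2.4 (Sample size) gives the basis of the calculation: "we chose an effect size of Cohen's *f* = .25 as a basis for power analysis". With 80% power and a 5% type I error rate, this "resulted in a required sample size of *N* = 86", and the effect to be found is described as follows: "to be able to detect medium sized between factor effects in a mixed design". The software is G*Power. No correlation between repeated measurements is given. Allowing for 20% dropout, 52 patients per group are to be recruited.

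Section 2.9 (Statistical analysis) sets up a mixed linear model with two groups and "the three-level within group factor time (assessments at T0, T1 and T2) for primary and secondary outcome measures". For the first research question, "the interaction between groups and time will be analysed to determine whether PTSD symptom severity differs for the intervention group". No power is given for that interaction.

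Section 2.7 (Procedure and assessment) places T0 before the intervention group gets access to the app.

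**The concern.** In a 2 × 3 mixed model the group main effect and the group × time interaction are separate F tests with different noncentrality and degrees of freedom. The main effect compares the arms on the average of all visits. The interaction asks whether the difference between arms changes over time. The power of one says nothing about the power of the other unless the pattern of differences over time and the correlation are also specified.

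In this trial the gap matters because T0 is a pre-treatment measurement in randomized arms. The expected difference there is zero, which dilutes the main effect but is exactly what gives the interaction its signal. At stake is the only justification given for the sample size. As written, it supports a test that is not used for the first research question.

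**Working it through.** **Inputs.** From section 2.4: f = .25, α = .05, power .80, N = 86. From section 2.5: 1:1 allocation. From section 2.9: 2 groups, m = 3 measurements. Assumed, because the article gives no value: common correlation ρ between visits, .5 for the reproduction (the program's default) and .3 to .8 as a range. With two equal groups, d = 2f = 0.5. All powers are from the noncentral F distribution, with equal variances and equal correlations across visits.

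**1. Reproducing N = 86.** Between-factor test: λ = f²·N·m / (1 + (m − 1)ρ), df 1 and N − 2.

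- N = 86: λ = .0625 × 86 × 3 / 2 = 8.06, power .8015.
- N = 84: λ = 7.875, power .792.

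So 86 is the smallest even N that reaches 80%, an exact match.

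**2. The interaction on the same inputs.** λ = f²·N·m / (1 − ρ), df 2 and 2(N − 2).

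- N = 28: λ = .0625 × 28 × 3 / .5 = 10.5, power .81. The required N would be 28.
- Other correlations give N = 54, 38, 18 and 12 (ρ = 0, .3, .7, .8). Two other scalings of the effect size give 82 and 80. None gives 86.

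Averaging over three visits is inferred from this match. Two measurements with ρ = .3 would give a between-factor N of 84, which is close. Either way it is a main-effect calculation, as the wording of section 2.4 says.

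**3. A medium effect that appears only after treatment.** Differences δ = (0, 0.5, 0.5) SD at T0, T1, T2; mean difference 1/3; N/4 = 21.5; ρ = .5.

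- Main effect: λ = 21.5 × (1/3)² / [(1 + 2ρ)/3] = 21.5 × .1111 / .6667 = 3.58, df 1 and 84, power .465.
- Interaction: Σ(δ − mean)² = 1/9 + 2 × 1/36 = 1/6, so λ = 21.5 × .1667 / .5 = 7.17, df 2 and 168, power .658.

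**4. The pattern that gives the stated 80%.** A constant 0.5 SD at all three visits gives the main effect λ = 21.5 × .25 / .6667 = 8.06, hence 80%. For the interaction, Σ(δ − mean)² = 0, so λ = 0 and power equals α, 5%. With no difference at T0, a three-visit mean of 0.5 SD would require 0.75 SD at T1 and T2, because (0 + .75 + .75)/3 = .5.

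**5. Range over ρ**, δ = (0, 0.5, 0.5), 86 analysed. The last two columns adjust for T0 as covariate: λ = 21.5 × .25 / (1 − ρ²) for T1 alone, and λ = 21.5 × .25 / [(1 + ρ)/2 − ρ²] for the mean of T1 and T2.

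| ρ | Main effect | Interaction | N for 80%, interaction | Adjusted, T1 | Adjusted, mean T1–T2 |
|---|---|---|---|---|---|
| .3 | .553 | .506 | 164 | .671 | .865 |
| .5 | .465 | .658 | 118 | .754 | .900 |
| .7 | .401 | .876 | 72 | .894 | .969 |
| .8 | .375 | .972 | 48 | .969 | .994 |

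If the effect halves by T2 (0, 0.5, 0.25), then at ρ = .5 the interaction has .527 and the adjusted mean .681.

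**The case against.** A reader might infer that the trial is underpowered and that a medium effect would be missed much more often than one time in five. The documents do not support that.

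- **The correlation is unknown.** At ρ = .7 or .8 the interaction exceeds 80% in the scenario above. The only PCL-5 correlation in the article is the test–retest value of .82 in section 2.8.1. That is a psychometric figure, not the correlation over 10 weeks to 6 months under treatment. Conversely, entry requires a PCL-5 above 33 (section 2.3), and restricting the baseline range tends to lower correlations with T0. Neither settles the value.
- **The scale of f is ambiguous.** If f = .25 was meant as the interaction effect in the program's own terms, 86 patients give power of about .9995.
- **The number analysed may exceed 86.** With all 104 retained by carrying the last observation forward, the same scenario gives at most .75 at ρ = .5 and .84 at ρ = .6. Carried-forward values would dilute the effect, so these are upper values. The planned covariates are also left out.

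These points stand, and they limit what can be said about the size and direction of the error.

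Two further defences carry less weight. Calling the study an exploratory pilot does not transfer a power figure from one test to another, and the article still derives its recruitment target from that figure. Nor is this a detail left to an analysis plan: the article states both the powered effect and the planned test, and they differ. It is also fair to say that the interaction is a valid test of differential change, so the inconsistency can be repaired without replacing it.

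**Conclusion.** The point holds as an inconsistency between sections 2.4 and 2.9. There is no slip of arithmetic: 86 is right for the test it was computed for. That test is not the one planned for the first research question, and this conclusion does not depend on the correlation.

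The consequence can be given only as a range. For 0.5 SD at T1 and T2 with 86 analysed, interaction power runs from 51% at ρ = .3 to 97% at ρ = .8. The 66% at ρ = .5 is one point in that range, resting on a default correlation and on equal differences at both visits. It is not a figure for the sponsor to print. Under the same scenario at ρ = .5, even the main effect that was powered reaches about 46.5%, not 80%.

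**What to change.** Restate the power in section 2.4 for the test that will be run. Give the assumed T0–T1–T2 correlation, the assumed differences at T1 and T2 in SD units and the number analysed, and show the power over a range of plausible correlations.

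Preferably, at the same N, make the primary test the group difference after baseline with T0 PCL-5 as covariate, either for the mean of T1 and T2 or for one named visit, and quote its power. For d = 0.5, 86 analysed and ρ from .3 to .7, that is about 86.5% to 97% for the mean and 67% to 89% for T1 alone. This uses data already planned.

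The cost is one rewritten paragraph and one model sentence, with no additional patients. If the interaction is kept, the stated power may turn out less favourable.

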## Abstract

**Background:** There is a great need for feasible interventions in the initial period after a trauma that minimize the risk of developing a clinically relevant PTSD. The majority of people suffer from severe sleep disorders after a traumatic event. Because sleep is essential for processing emotional memories, we aim to improve sleep quality in acutely traumatized patients to benefit adaptive trauma processing and thereby prevent PTSD development.

**Objective:** In a multicentre randomized controlled trial (RCT), we will investigate whether digital cognitive behavioural therapy for insomnia (dCBT-I) has the potential to not only increase sleep quality in acutely traumatized individuals but also reduce trauma-related symptoms (specific PTSD symptoms as well as related symptoms such as depression, anxiety and functional outcomes) and the risk for PTSD development in acutely traumatized individuals. Moreover, we will test if sleep disturbances pre-therapy predict the development of later PTSD symptoms.

**Method:** We aim to recruit 104 patients who will be randomly assigned to an app-based sleep intervention utilizing CBT-I or a sleep diary as an add-on to treatment-as-usual (TAU) in outpatient acute trauma centres. Sleep quality, PTSD symptoms and everyday functioning will be measured before, after the intervention and at a 6-month follow-up.

**Conclusion:** To our knowledge, this multicentre RCT is the first study to use dCBT-I as an early intervention for trauma. It may improve the understanding of the role of sleep in the development of PTSD and has the potential to contribute to the development of an easy-to-use early intervention for acutely traumatized individuals.

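### Minor arithmetic error in the dropout allowance: 86 required at 20% dropout calls for 108 recruits, not 104, and completer power is about 79% rather than 80%

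*Protocol article*

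**What the plan says.** Section 2.4 (Sample size) of the protocol article takes Cohen's f = .25 "as a basis for power analysis and sample size calculation". With 80% power and a 5% type I error rate it arrives at N = 86, which it says is enough "to be able to detect medium sized between factor effects in a mixed design".

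The same section then turns to attrition: "Considering a dropout rate of 20% from guideline-recommended psychological treatments for post-traumatic stress disorder". It calls this rate an orientation and sets 52 participants per group. The Abstract gives the matching total: "We aim to recruit 104 patients". The step from 86 to 104 is not written out.

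Section 2.9 (Statistical analysis) plans an intention-to-treat analysis, in which dropouts stay in by last observation carried forward, and a per-protocol analysis. The model has a two-level group factor and a "three-level within group factor time (assessments at T0, T1 and T2").

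**The concern.** A dropout rate is the share of recruited participants who are lost. To end with a required number, one divides that number by the share retained (0.80). Multiplying by 1.20 adds 20% of the smaller, final number, which is less than 20% of the number recruited. The target of 104 is what the multiplication gives.

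The three figures in section 2.4 (86 needed, 20% lost, 104 recruited) therefore do not fit together. At stake is whether the design delivers its stated 80% power on its own inputs, and whether a reader can rely on 104 as a target that absorbs a 20% loss.

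**Working it through.** **Inputs.** From section 2.4: f = 0.25, alpha = 0.05, power 80%, required N = 86, dropout 20%, 52 per group. From section 2.9: 2 groups and 3 time points (m = 3). From section 2.5 (Randomization): 1:1 allocation. The correlation among repeated measures (rho) is not stated; 0.5 is assumed, with a range shown in step 4.

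**1. Reproduce the 86.** For the between factor in a repeated-measures ANOVA, the F statistic has (1, N - 2) degrees of freedom and noncentrality

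lambda = f² x N x m / (1 + (m - 1) x rho).

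- N = 86: lambda = 0.0625 x 86 x 3 / (1 + 2 x 0.5) = 16.125 / 2 = 8.0625; power 80.15%.
- N = 85: power 79.7%.

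So 86 is the smallest number that reaches 80%, and the plan's figure is reproduced. Of the correlations 0.3, 0.5, 0.7 and 0.8 with three measurements, only 0.5 returns 86; the others return 70, 104 and 112.

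**2. The dropout step.**

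- Dividing: 86 / (1 - 0.20) = 107.5, so 108 in total; per group 43 / 0.80 = 53.75, so 54.
- Multiplying: 86 x 1.20 = 103.2, so 104 as an even number; per group 43 x 1.20 = 51.6, so 52.

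The plan's 52 per group agrees with the second line. That this was the route taken is inferred from the figures. The next step does not depend on it.

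**3. What 104 delivers.**

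- Remaining at 20% loss: 104 x 0.80 = 83.2, about 83, against 86.
- Dropout that 104 can absorb: 1 - 86/104 = 0.173, about 17%.
- Power at N = 83: lambda = 0.0625 x 83 x 3 / 2 = 7.78; power 78.7%. This is 1.3 points below 80%, and 1.4 points below the 80.15% at N = 86.

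**4. Dependence on the assumed correlation** (same formula, N = 86 and then N = 83):

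| rho | power at 86 | power at 83 |
|---|---|---|
| 0.3 | 88.1% | 86.9% |
| 0.5 | 80.15% | 78.7% |
| 0.7 | 72.7% | 71.1% |
| 0.8 | 69.2% | 67.6% |

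The level moves with rho, but the loss from 86 to 83 stays between 1.2 and 1.6 points. Only rho = 0.5 is consistent with the plan's own 86. The shortfall in participants (83 against 86) needs no correlation at all.

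**The case against.** The best defence is that nothing of substance changes. The gap is 4 recruits, about 3 completers and little more than one point of power, in a study that describes itself as an exploratory pilot. The 20% is borrowed from PTSD treatments and offered only as an orientation, and the section never promises 86 evaluable participants. All of this stands and fixes the severity at minor. It does not make the figures agree: 20% is the only rate given, and no other reason for 104 is offered.

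A second defence is that the intention-to-treat analysis includes all 104, where the formula gives a nominal 87.1%. That limits the point to participants with observed outcomes and to the per-protocol analysis. The 87.1% is not a true power, however, because carried-forward values do not restore the lost follow-up information. The authors' own attrition allowance also treats 86 as the number needed after dropout.

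Two stronger readings are tempting and not supported. A reader might infer that the trial as a whole misses its power; the documents show a shortfall only for completers at a loss of 20%. A reader might also take the app's "completion rates of 68" per cent in section 2.6.1 (Intervention group) as a worse attrition rate for planning. That figure describes completion of the app programme, which only one arm receives. Outcomes are collected by separate online questionnaires sent to everyone (section 2.7), so a participant who stops using the app can still be assessed. Choosing another source for attrition would be a preference, not the correction of an error.

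**Conclusion.** The point holds as a minor arithmetic error. On the plan's own 86 and 20%, the target should be 108 (54 per group). The stated 104 leaves about 83 participants with observed outcomes and allows for about 17% dropout. Completer power is about 78.7% instead of 80%.

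The head counts follow from the stated figures alone. The power figure rests on f = .25, three measurements and an assumed correlation of 0.5. It refers to the between-factor effect for which section 2.4 sized the study, and should not be read as the power of any other test in section 2.9.

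**What to change.** In section 2.4, restate the result in one sentence. Either say that 104 recruited gives about 83 completers at 20% dropout and about 79% power for the stated between-factor effect, or say that 104 allows for about 17% dropout at 80% power. Give the correlation used, so that the figure can be checked.

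The cost is one sentence and a slightly lower stated power or dropout allowance. Recruitment and the Abstract stay as they are. Only if the sponsor prefers to keep both 20% and 80% does the target become 54 per group (108), which means 4 more recruits and a matching change in the Abstract.
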